### Sample size

Comparisons of primary interest are comparing outcome 1 (treatment commencement) in control and arm A; outcome 1 in control and arm B; and outcome 2 (HCV cure) in control and arm C. We consider sample size calculations with a minimum of 80% power and a significance level of 0.05/3=0.0167. Comparisons of control versus A are expected to result in the smallest required sample sizes so sample size calculations focus on this comparison. We use the Shiny CRT app^36^ for sample size calculations, assuming that the t- distribution is used instead of the normal approximation (accounting for small numbers of clusters).^37^

We suppose that five sites are assigned to each of the six treatment sequences. We found that with 24 participants recruited in each cluster in each period, power will be greater than 80% to detect a change in proportions of participants starting HCV treatment of 30%–50% where 10 clusters are allocated to arm A. Due to the greater portion of participants expected to start treatment in arm B (70%) and arm C (90%), power >80% is achieved with eight clusters assigned to the sequences that involve arms B or C (ie, with four clusters randomised to each of the arm B then control; control then arm B; Arm C then control; and control then arm C sequences). The proportion of participants expected to achieve cure in each arm are 10% among controls, 30% in arm A, 50% in arm B and 70% in arm C. Allowing for 20% loss to follow-up of sites and of participants, 30 participants per site per period would need to be recruited. Given these results, we will instruct sites to aim for 40 participants per site per period to counteract instances where some sites are unable to achieve 30 participants per site per period; some sites achieving 40 participants will balance sites which achieve <30. This would imply a maximum total of 2400 participants would need to be recruited.

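### The 30 per site-period covers 20% participant loss only; for arm A no allowance for losing 20% of sites is shown

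*Protocol article*

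**What the plan says.** All the relevant statements are in the Sample size section of the protocol article.

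- The criteria are set by "We consider sample size calculations with a minimum of 80% power" and "a significance level of 0.05/3=0.0167". The calculation is said to focus on control versus arm A.
- Five sites are planned for each of six sequences.
- For arm A: "with 24 participants recruited in each cluster in each period, power will be greater than 80" per cent, "to detect a change in proportions of participants starting HCV treatment of 30%–50% where 10 clusters are allocated to arm A".
- For the other two arms: "power >80% is achieved with eight clusters assigned to the sequences that involve arms B or C", on the ground that larger proportions are expected to start treatment there.
- The loss allowance follows: "Allowing for 20% loss to follow-up of sites and of participants, 30 participants per site per period would need to be recruited".
- Sites are then told to aim for 40 per period. The reason given is that some sites may not reach 30; site loss is not mentioned. From this comes "a maximum total of 2400 participants would need to be recruited".

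**The concern.** The loss sentence names two losses, of sites and of participants, each at 20%, and offers one figure as the allowance for both. That figure is fully explained by one of them. The site loss would then have to be absorbed by the number of sites. For arms B and C it is. For arm A the only power statement uses every planned site.

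A steering committee or monitoring board reading this section would conclude that the loss of six of 30 sites is already budgeted for. For A versus control, nothing stated supports that conclusion.

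**Working it through.** **Inputs from the article.** 24 per cluster-period; 30% versus 50%; alpha 0.05/3 = 0.0167 (taken as two-sided, since sidedness is not stated); t-distribution (degrees of freedom not stated); 5 sites x 6 sequences = 30 sites, so 10 per intervention arm; 20% loss of sites and of participants; target 40.

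**Assumed, because the article gives none.** ICC, CAC and degrees of freedom. K is the number of sites in the A/control pair.

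**1. The plan's own figures**
- 24/(1 - 0.20) = 30. The stated figure reproduces exactly from participant loss alone.
- 30 sites x 2 periods x 40 = 2400. This also reproduces.

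**2. What both losses would require**
- Through numbers per site-period: 24/(0.8 x 0.8) = 37.5.
- Through the site count for arm A: 10/0.8 = 12.5 sites, against 10 planned.

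**3. What remains after both losses at 30 per site-period**
- Sites: 30 x 0.8 = 24, or 8 per arm. Eight is the number stated as enough for B and C.
- Arm A: 8 x 24 = 192 evaluable per condition, against 10 x 24 = 240 planned.

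**4. Power for arm A in an isolated two-period cross-over comparison**

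Design factor: DE = 1 + (m - 1) x ICC - m x ICC x CAC.
Variance of the difference: [p1(1 - p1) + p2(1 - p2)] x DE/(K x m), with 0.21 + 0.25 = 0.46.
Power is taken from the non-central t with non-centrality 0.20/SE.

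At ICC 0.05 and CAC 0.8:
- m = 24: DE = 1 + 1.15 - 0.96 = 1.19.
- K = 10: SE = sqrt(0.46 x 1.19/240) = 0.0478, non-centrality 4.19.
- K = 8: SE = sqrt(0.46 x 1.19/192) = 0.0534, non-centrality 3.75.

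| Reference distribution | 10 sites x 24 | 8 sites x 24 |
|---|---|---|
| t, K-2 df | 84.5% | 67% |
| t, K-1 df | 86% | 72% |
| t, 2K-2 df | 93% | 83% |
| normal | 96% | 91% |

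Range: take the 30 combinations of ICC 0.01, 0.02, 0.05, 0.10, 0.15, 0.20 with CAC 0.5, 0.7, 0.8, 0.9, 1.0.
- With K-2 df, ten sites reach 80% in 20 combinations. Eight sites fall below 80% in 17 of those.
- With 2K-2 df, ten sites reach 80% in 24. Eight sites fall clearly below in five, and one more sits at 80.0%.

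**5. Power for arm A in the planned model**

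The Statistical analysis section pools controls across arms in one model. A linear generalised least-squares approximation was run with all three arms, a period effect, random clinic and clinic-period effects, 24 surviving sites, 24 evaluable per cell and 20 df.
- At ICC 0.05 and CAC 0.8 it gives about 93% for arm A.
- Over ICC 0.01 to 0.10 it falls below 80% only at ICC 0.10 with CAC 0.5 (71%). There the isolated ten-site calculation also fails (58% with K-2 df, 69% with 2K-2).

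**6. If every remaining site reached 40**
- 40 x 0.8 = 32 evaluable, and 8 x 32 = 256 against the planned 240.
- DE = 1 + 1.55 - 1.28 = 1.27, and SE = sqrt(0.46 x 1.27/256) = 0.0478, the same as ten sites at 24.
- With K-2 df, power is still 78% rather than 84.5%, because 6 df replace 8.

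**The case against.** The strongest case on the other side has four parts.

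- **The article never calls ten a minimum for arm A.** It says that power exceeds 80% "where 10 clusters are allocated to arm A" and is silent on eight. This stands. A reader might infer that arm A misses 80% after the stated site loss. The documents do not show that, because the ICC, CAC and degrees of freedom are absent and eight sites stay above 80% under plausible choices.
- **The low figure depends on a severe choice of degrees of freedom and on isolating one pair of conditions.** This also stands. K-2 leaves 6 df with eight sites, whereas the planned model also draws on control periods at the B and C sites. The 67% is the low end of the worked example and should not be quoted alone.
- **A site allowance does exist for two of the three comparisons.** Eight of ten is exactly a 20% margin for B and C. This stands and limits the point to arm A.
- **The target of 40 exceeds 37.5.** True, but the article justifies 40 by shortfalls in recruitment and expects sites above 30 to offset sites below. It does not repair a sentence that assigns the allowance to 30.

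It can also be said that a journal article may leave the ICC and CAC to the full protocol. Their absence is not the finding. The finding is that a stated allowance does not follow from the figures beside it.

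**Conclusion.** The point holds in a limited form. The sentence is wrong as written: 30 contains the participant allowance and nothing for sites. The site count supplies the missing margin for B and C. For arm A, the comparison on which the calculation focuses, no allowance is shown, and after both losses its evaluable number per condition would be 192 rather than 240.

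The effect on power is undetermined from the article. At the assumed ICC of 0.05 and CAC of 0.8, arm A with eight sites has about 67% (t, K-2 df) to 83% (t, 2K-2 df) in isolation, and about 93% in the linear approximation of the pooled model. The arithmetic on 30 and 37.5 rests on no assumption beyond reading 24 as the number needed for analysis, which 24/0.8 = 30 implies.

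**What to change.** Restate the loss sentence so that 30 per site-period allows for 20% participant loss only, and say that the site margin (eight of ten) applies to arms B and C.

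Add arm A power with eight sites and 24 evaluable per period, under the ICC, CAC and degrees of freedom that were actually used. If the figure relies on pooled controls, say so.

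Note that the target of 40, if the remaining sites reach it, restores arm A's participant count (256 against 240) but not the lost clusters.

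The cost is a few lines of text and one rerun of the authors' own calculation. No extra sites or participants are asked for. The stated robustness for arm A may turn out less favourable than the present sentence suggests.

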### Statistical analysis

Results from the trial will be reported according to the CONSORT extension statement for cluster randomised trials,^38^ or a CONSORT extension statement for cluster randomised crossover trials if one is available prior to end of data collection. Clinic and patient demographics will be described by site and study period. Analyses will be conducted on an intention-to-treat basis, with patients analysed according to the randomised treatment of their cluster at the time of their inclusion in the study. All available binary outcomes will be analysed at the patient level using mixed-effects logistic regression models with random intercepts for clinic and clinic period and fixed effects for interventions.^39^ ORs and 95% CIs will be reported; in addition, we will calculate and report risk differences and 95% CIs.

There are three main comparisons proposed, namely, treatment uptake outcome in arm A versus control (comparison 1) and arm B versus control (comparison 2) and HCV cure in Arm C versus control (comparison 3). Incremental benefits of arm B to arm A, and arm C to arm B, and arm C to arm A on treatment uptake and HCV cure will be performed in subgroup analyses. Data from controls in each arm will be pooled and a single model fitted for each outcome.

Randomisation will occur in batches of six, performed by the coordinating centre and concealed from investigators and sites until after site governance approcal. Since randomisation is occurring within batches of six services, fixed effects for batch will be included in these models. The Kenward-Roger correction will be applied to adjust for the small number of clinics.^40^ Estimates of intracluster correlations (within-period and between-period) will be reported. Time-to-event outcomes such as time to complete diagnosis will be analysed using Cox proportional hazards models with shared-frailty terms for site and fixed terms for treatment group and randomisation batch. There may be imbalances between sites with respect to various clinic and patient-level characteristics, and secondary analyses will adjust for these.

Sensitivity analyses to investigate the impact of different assumptions about missing data on study conclusions will be performed. Initially, two scenarios will be considered: ‘best-worst’ and ‘worst-best’. In the ‘best-worst’ scenario, all patients with missing data in clinics during periods of administration of arms A, B or C will be assumed to have commenced HCV treatment, and all patients in control periods will be assumed not to have commenced HCV treatment. In the ‘worst-best’ scenario, all patients with missing data in clinics during periods of administration of arms A, B or C will be assumed to not have commenced HCV treatment, and all patients in control periods will be assumed to have commenced HCV treatment. Similar scenarios for the SVR outcome will be considered. Should these analyses lead to different study conclusions, further analyses including terms predictive of missingness will be conducted or using multiply imputed datasets will be considered.

## Ethics and dissemination

### Ethical review

This study has been approved by the Alfred Ethics Committee (Number: HREC/64731/Alfred-2020-217547). Informed consent will be obtained from all participants prior to enrolment. Potential participants will be presented with detailed information about the study procedures, objectives, risks and benefits. Participants will be able to refuse or terminate participation at any time. Participants will be reimbursed US$40 at their baseline visit and US$80 for their SVR visit. Reimbursement will be by Coles/Myer voucher or by direct funds bank transfer (EFT/PayID).

### Data monitoring

The trial will be monitored by an independent data safety and monitoring board with an independent statistician. There will be predefined periodic analysis to assess safety endpoints (drug resistance among treatment commencing participants, treatment failures, serious adverse events as detailed below) in accordance with a statistical analysis plan under development before conclusion of recruitment. Access to identified study data will be limited to the data manager and study coordinator. Deidentified data will be limited to study investigators.

### Adverse events

This study uses a drug with side effects that are already known. It will, therefore, report adverse events that, in the opinion of the investigator, are not deemed to be expected or are increased in severity from prior observations. Side effects not already known of the drug in a severity that the treating investigator deems as unexpected/serious should be reported to Burnet Institute as sponsor.

For this study, we will only be collecting adverse events that are inconsistent with prior observations reported in study drug product information. Adverse events considered to be related to study drug administration will be captured up until 24 weeks after the last recorded study dose.

Serious adverse events will be reported to the Burnet as sponsor within 24 hours of the site learning of them and include any event that results in death; threat to life; significant disability or incapacity; congenital abnormality or birth defect; hospitalisation or is medically significant and requires intervention to prevent any of the former outcomes.

Burnet Institute is responsible for reporting safety events to the reviewing HREC in accordance with Safety Monitoring and Reporting in Clinical Trials Involving Therapeutic Goods (NHMRC, 2016).

In line with the Alfred Hospital Ethics Committee Safety Monitoring and Reporting Requirements (October 2017), only events that meet the criteria of a significant safety issue and/or urgent safety measure will need to be reported to the Alfred HREC.

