##### Weeks 1–2 (confirmatory results)

Participants will be contacted with the results of their confirmatory laboratory blood tests. Participants with a positive confirmatory antibody and negative RNA test result will be contacted with this result of prior exposure, no current infection and instructed to discontinue treatment and dispose of any unused medications. They will complete the study here. Standard harm minimisation messaging and window periods for detection of HCV will be discussed with the participant.Participants with a positive confirmatory antibody and positive confirmatory RNA result will be contacted to arrange ongoing treatment through the study, a further 4 weeks of sofosbuvir/velpatasvir will be dispensed. Further assessment may be required based on the laboratory blood test results:If the participant received an Aspartate Animotransferaese (AST):Platelet Ratio Index score of <1.0, they will be instructed to continue treatment as they were originally instructed.If the participant received an AST:Platelet Ratio Index score of ≥1.0, they will be instructed to continue taking the DAAs and will be referred to a specialised.Participants found to have renal impairment (estimated glomerular filtration rate (eGFR) <30 mL/min) or coinfected with chronic hepatitis B will be instructed to cease treatment and will be referred to a specialist.Participants found to have HIV infection will be instructed to continue the DAAs and be referred to a specialist.

Following specialist assessment, the participant may be required to change medications or alter their treatment course, according to the specialist’s recommendations.

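### The adverse event rules cannot all be followed: a known serious event is both excluded from collection and reportable within 24 hours

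*Protocol article*

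**What the plan says.** The Adverse events section contains five statements about what is recorded or reported.

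- (a) Because the drug's side effects are known, the study will "report adverse events that, in the opinion of the investigator, are not deemed to be expected or are increased in severity from prior observations".
- (b) On what goes to the sponsor: "Side effects not already known of the drug in a severity that the treating investigator deems as unexpected/serious should be reported".
- (c) On collection: "we will only be collecting adverse events that are inconsistent with prior observations reported in study drug product information".
- (d) On related events: "Adverse events considered to be related to study drug administration will be captured up until 24 weeks after the last recorded study dose".
- (e) On serious events: "Serious adverse events will be reported to the Burnet as sponsor within 24 hours of the site learning of them". The definition that follows, "of the site learning of them and include any event that results in death", goes on to list the other seriousness criteria, hospitalisation among them. It carries no condition on expectedness or relatedness.

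The Data monitoring section relies on these rules for the safety board: "There will be predefined periodic analysis to assess safety endpoints (drug resistance among treatment commencing participants, treatment failures, serious adverse events as detailed below".

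In arm C, the Baseline visit section has antibody-positive participants start a 14-day supply before the laboratory has confirmed the diagnosis. Under Weeks 1–2 (confirmatory results), those found RNA negative are told to stop. Those with eGFR below 30 mL/min or "coinfected with chronic hepatitis B will be instructed to cease treatment and will be referred to a specialist".

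**The concern.** Statement (c) is absolute and does not exempt serious events. Statement (e) is equally absolute in the other direction. A site faced with a serious event that the product information already lists has one sentence telling it not to collect and another telling it to report within a day.

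Two things are at stake. The first is whether the safety board's serious adverse event data are complete. Statements (a) and (b) leave expectedness to the local investigator, so different sites could settle the conflict differently and nothing in the data would show it.

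The second is what the trial can say about the safety of presumptive treatment. The filter is justified on the ground that the drug is well characterised. What is new in arm C is the strategy: some people take the drug without current infection, and others before a renal or hepatitis B result that leads to an instruction to stop. How often even familiar effects occur in these people is part of what the strategy costs them.

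**Working it through.** No arithmetic applies. The check is to take five kinds of event and ask what each collection or reporting sentence, (b) to (e), requires.

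| Event in a participant given study drug | (b) sponsor, unknown effects | (c) collection | (d) related, to 24 weeks | (e) serious, 24 hours |
|---|---|---|---|---|
| Serious, related, not listed | send | collect | capture | report |
| Serious, related, listed, usual severity | do not send | do not collect | capture | report |
| Serious, judged unrelated | not a side effect, so not sent | unclear | not covered | report |
| Non-serious, related, not listed | send if deemed unexpected | collect | capture | not covered |
| Non-serious, related, listed, usual severity | do not send | do not collect | capture | not covered |

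The sentences agree on events that are related and not listed. They also do not exclude a known effect that is worse than previously observed, because (a) keeps it reportable. They disagree in the second and fifth rows, and the third is left unclear.

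1. **Second row.** Statements (b) and (c) leave the event out; (d) and (e) bring it in. Since (b) and (e) name the same recipient, this is not a matter of two separate reporting lines.
2. **Fifth row.** Read at face value, (d) captures what (c) says is not collected.
3. **Safety board.** Data monitoring points forward to the Adverse events section for its serious events. If sites follow (e), the board sees all of them. If sites follow (c), it sees only those judged inconsistent with the product information. This follows from the second row and is not a separate contradiction. The board's other two endpoints, resistance and treatment failure, are unaffected.
4. **Arm C.** Suppose (e) governs every serious event and (c) governs the rest. Expected non-serious events are then still not collected, so their frequency cannot be reported for participants dosed before RNA, eGFR and hepatitis B results. That gap remains on the most favourable reading.

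**The case against.** The strongest reply is that the section has two tiers. It deals first with ordinary adverse events and known effects, then opens a separate paragraph on serious events with its own definition and deadline. On that reading (c) governs non-serious events, (e) governs serious ones, and only a statement of scope is missing. The 24-week sentence can likewise be read as a time window for events that pass the filter. The board's remit refers to the unfiltered definition. Not counting expected non-serious effects of a known drug is a stated choice with a stated reason.

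Much of this is fair. The two-tier reading is plausible and may be what was intended. But it is not what the text says: (c) is unqualified, and (b) carries the same restriction into a sentence about events deemed unexpected or serious. Nor is this detail that an article leaves to the full protocol, since the article itself states rules that conflict.

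A reader might go further and infer that the board will receive only unexpected serious events, or that the filter discards the known harms of early dosing. The document supports neither. Serious events reach the sponsor if (e) is followed, events of increased severity stay reportable, and the product information is not shown, so no particular harm can be classed as listed. Nor should the arm C argument be widened. Drug interactions are reviewed before dosing, and participants found to have HIV or an APRI score of 1.0 or more are told to continue with referral.

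**Conclusion.** The point holds as an unresolved conflict in the collection rules. For serious events, (c) and (e) cannot both be followed when the event is listed in the product information, and no precedence is given. The effect on the safety board is conditional: its serious adverse event analysis could be incomplete if sites apply (c) to serious events, and is complete if they apply (e). For non-serious events the consequence is definite if (c) is followed: the frequency of expected ones under presumptive treatment in arm C will not be known.

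The size cannot be put as a number. The article gives neither the number of participants expected to be dosed in arm C nor an expected rate of serious or listed events, so any bound would rest on an assumed antibody prevalence and would not measure this defect. The serious-event conflict must be resolved because it affects the completeness of the safety data. The non-serious gap is the lesser part and can be accepted if it is declared.

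**What to change.** Reconcile the Adverse events section as follows.

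- State that all serious adverse events in participants given study drug are collected and passed to the safety board, regardless of expectedness or relatedness.
- Restrict the product-information filter to non-serious events, and amend statements (b) and (c) to say so.
- Use expectedness only to decide onward or expedited reporting, not whether an event is recorded.
- State whether the 24-week sentence is a time window for events that pass the filter or a separate rule capturing all related events.
- Optionally, record events that lead to stopping study drug in arm C.
- If the filter stays for non-serious events, say in the trial report that their frequency under presumptive treatment was not measured.

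This changes data collection and reporting only, not clinical management. It costs protocol and case report form wording and some additional serious adverse event forms, including background hospitalisations unrelated to the drug. Recruitment began on 9 March 2022 and was expected to finish in December 2024. For participants already dosed under the current wording, capture can only be retrospective, from medical records, and may be incomplete. The report should distinguish events found that way from those recorded prospectively.
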